### Time course of the study

#### Preoperative assessment and admission

During standard institutional preoperative assessment, the patient’s eligibility for radical cystectomy and urinary diversion will be evaluated. Medical history, laboratory and chest X-ray or computed tomography (CT) scan, 12-lead electrocardiogram (ECG), ASA physical status, BMI, Respiratory Failure Risk Index (RFRI), nutritional risk screening (NRS 2002 tool) and, if required (in case of history of smoking or coronary artery disease), results of spirometry, echocardiography and ergometry will be recorded. Participants fulfilling the inclusion criteria will be asked for their signed informed consent.

After admission to the Department of Urology (on the day before surgery) a central venous catheter will be placed, a blood sample will be taken from included patients for baseline levels of PCT (T_0_), a chest X-ray will be performed and, if there are no exclusion criteria, patients will be randomized into one of the study groups. Patients will be given oral carbohydrate loading (maltodextrin) 12, 8 and 2 h before surgery, 1000 mL of crystalloid solution will be given and antimicrobial prophylaxis will be introduced using ciprofloxacin and metronidazole 30 min before surgical incision. Antimicrobial prophylaxis will be continued for 72 h (2 × 400 mg ciprofloxacin and 3 × 500 mg metronidazole per day). Deep vein thrombosis prophylaxis will be carried out using low-molecular-weight heparin (LMWH).

#### Intraoperative care

Before induction of anesthesia an epidural catheter and an arterial cannula will be inserted for invasive arterial blood pressure monitoring and blood gas sampling.

Immediately after induction of anesthesia and orotracheal intubation, once a steady state has been reached (Table 2), all patients will be submitted to an ARM using the sustained airway pressure by the CPAP method, applying 30 cmH_2_O PEEP for 30 s. After ARM, PEEP will be set to 6 cmH_2_O in the CG (“standard PEEP”) and LPV (TV = 6 mL/Kg IBW, FiO_2_ = 0.5) will be performed. In the SG (“optimal PEEP”) PEEP will be determined during a Cstat-directed decremental PEEP titration procedure. During surgery ARM will be repeated and arterial and central venous blood gas samples (ABGs, CVBGs) will be evaluated every 60 min. In case of decreased oxygen saturation (SpO_2_ < 94%) rescue ARM will be performed using a FiO_2_ of 1.0. PCT levels will be measured 2, 6, 12, 24, 48 and 72 h after surgical incision.

**Table 2 Tab2:** Steady state after induction of anesthesia

	Parameter	Value
Hemodynamics	Mean arterial pressure	65 mmHg < MAP < 90 mmHg
	Heart rate	50/min < HR < 100/min
Ventilation	SpO_2_	≥96%
	EtCO_2_	35–40 mmHg
Anesthetics	EtSevo	1.0 MAC

*MAP* mean arterial pressure, *HR* heart rate, *SpO*
_*2*_ peripheral capillary oxygen saturation, *EtCO*
_*2*_ end-tidal carbon dioxide partial pressure, *EtSevo* end-tidal sevoflurane concentration, *MAC* minimal alveolar concentration

Arterial blood pressure, heart rate (HR) and end-tidal carbon dioxide tension (EtCO_2_) will be monitored continuously. Cstat, airway resistance (Raw), Vds/Vt, core temperature and train-of-four relaxometry data will be recorded every 15 min.

During surgery, in cases of hypotension, intravenous norepinephrine will be started to maintain mean arterial pressure above 65 mmHg. For intraoperative fluid management patients will receive 3 mL/Kg/h of balanced crystalloid solution until end of surgery. In cases of bleeding, a 200-mL colloid (hydroxyethyl starch, HES) solution bolus and crystalloid substitution will be given. Packed red blood cell (PRBC) transfusion will be given whenever the attending anesthetist feels it necessary.

#### Postoperative care

After extubation, patients will be admitted to the ICU. ABGs and CVBGs will be collected and evaluated (pH, base excess (BE), standard bicarbonate (stHCO^3−^), ScvO_2_), PaO_2_/FiO_2_ and central venous-to-arterial carbon dioxide gap (dCO_2_) will be calculated every 6 h until 72 h after surgery. On the first postoperative day (POD), a chest X-ray will be performed and repeated on the following days if the development of pulmonary complications are suspected. The chest X-ray will be evaluated by an independent, trained radiologist who will not be involved in the study. Continuous epidural analgesia and intermittent intravenously administered analgesia (paracetamol or metamizol) will be introduced, and evaluated effective if a Numeric Pain Rating Scale (NPRS) score is lower than 3 points.

During postoperative care, continuous intraabdominal pressure (IAP) monitoring via a direct intraperitoneal catheter, placed before closure of the abdominal wall, will be performed to eliminate bias caused by the elevation of IAP.

Patients’ clinical progress and secondary endpoints will be monitored by daily SOFA scores, laboratory and physical examinations.

Postoperative hydration and vasopressor therapy will be directed by MAP, ScvO_2_, dCO_2_ and arterial lactate levels. PRBC units will be transfused if decreased hemoglobin (Hb) levels result in tissue oxygenation disorders or become symptomatic (hypotension, dizziness or weakness develop). Fresh frozen plasma will be given if the prothrombin International Normalized Ratio (INR) > 1.5. Platelet suspension units will be given according to the Transfusion Guidelines of the Hungarian National Blood Transfusion Service.

In both groups, patients will be allowed to drink clear fluids immediately after surgery and the use of chewing gum will be encouraged. Prokinetics and an oral liquid diet using a drinking formula will be started on POD 1 and patients will begin active mobilization. The nasogastric tube will be removed on the morning of POD 1.

#### From postoperative day 4 (POD 4 to POD 28, follow-up)

During the follow-up period, secondary endpoints, in-hospital stay, 28-day and in-hospital mortality will also be evaluated.

Figure 2 shows the CONSORT flowchart of the trial.

**Fig. 2 Fig2:**
[figure not shown]
Consolidated Standards of Reporting Trials (CONSORT) flowchart. *PEEP* positive end-expiratory pressure, *PCT* procalcitonin, *ABGs* arterial blood gas sample, *CVBGs* central venous blood gas sample, *Cstat* static pulmonary compliance, *Vds/Vt* dead space fraction, *Raw* airway resistance, *MAP* mean arterial pressure, *ARM* alveolar recruitment maneuver*, PRBC* packed red blood cell, *FFP* fresh frozen plasma, *IAP* intraabdominal pressure

### Study arms and assigned intraoperative interventions

A total number of 40 patients with bladder cancer submitted to general anesthesia and open radical cystectomy and urinary diversion will be enrolled in this study. An equal number of patients will be randomized into the two groups.

Patients randomized into the SG group undergo an alveolar recruitment maneuver using the sustained airway pressure by the CPAP method, applying 30 cmH_2_O PEEP for 30 s followed by a decremental PEEP titration procedure directed by Cstat. During the PEEP titration procedure, PEEP will be decreased from 14 cmH_2_O by 2 cmH_2_O every 4 min, until a final PEEP of 6 cmH_2_O is reached. On each level of PEEP, ABGs will be collected and evaluated. Optimal PEEP is considered as the PEEP value resulting the highest possible Cstat measured by the ventilator. After the PEEP titration procedure, lung-protective mechanical ventilation will be performed using optimal PEEP and low tidal volumes and ARM will be performed every 60 min.

Patients randomized into the CG group will undergo an alveolar recruitment maneuver using the sustained airway pressure by the CPAP method, applying 30 cmH_2_O PEEP for 30 s followed by low-tidal-volume LPV using a PEEP value of 6 cmH_2_O and ARM will be repeated every 60 min.

### Data monitoring

Data monitoring will be performed centrally for quality control purposes by an external, independent physician, who will not be involved in the study. Monitoring will evaluate the progress of the study and verify the accuracy and completeness of the data recording (CRF, source data, Informed Consent Forms and outcome variables).

### Statistics

Data will be analyzed by the research team in collaboration with a medically versed biostatistician after completion of the trial. There will be no interim analysis. Statistical analysis will be conducted on an intention-to-treat basis. IBM SPSS 20.0 statistical software will be used for analysis.

It is expected that the majority of source data will be recorded onto CRF; nonetheless, before starting the data analysis, the mechanism and pattern of missing data will be evaluated and these findings will be used to determine whether they have had an impact on the statistical analysis and results and how they can be managed.

Data distribution will be tested by the Kolmogorov-Smirnov analysis. Normally distributed data will be presented as mean and standard deviation (SD) and skewed data as median (interquartile range). Comparing related samples, the paired and unpaired *t* test will be used for normally distributed data and the Wilcoxon signed rank test and Mann-Whitney *U* test for skewed data. Differences in proportions will be evaluated using the Fisher’s exact test, and risk ratio with associated 95% confidence interval (CI). Analysis of the primary endpoint (PPC) will be carried out by the unpaired Student’s *t* test (95% CI). A two-way, repeated-measures analysis of variance (two-way RM ANOVA) will be used to compare the groups’ serum PCT levels. The relationship between PCT levels and organ dysfunctions will be evaluated using the Pearson correlation. Statistical analysis of SOFA scores, ICU days, in-hospital stay, in-hospital and 28-day mortality data of groups will be implemented by the chi-square test. A *P* value < 0.05 will be considered significant.

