### Blinding, data collection, randomization and record-keeping

This is a single-blinded (participant) study. Patient data, intraoperative and postoperative measurements, fluid balance, respiratory parameters, laboratory results and clinical status (Sequential Organ Failure Assessment (SOFA) score) will be collected onto Case Report Forms (CRF). CRF and the patient evaluation chart will not be assessed in front of the patient.

Participants will be randomized to the SG or CG in a ratio of 1:1. Randomization will be carried out by a computer-generated blocked randomization list with 10 blocks of four patients per block. Allocation will be stored in sealed, opaque and numbered envelopes. Participants will be included and allocated in numerical order.

All original records (CRF and relevant correspondence) will be archived and secured for 15 years, and then destroyed according to the hospital standards concerning destruction of confidential information.

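### A Kolmogorov-Smirnov pre-test at about 20 per arm decides how continuous data are summarised, and which test is used where none is named: a minor weakness that wording can remove

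*Protocol article*

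**What the plan says.** The Statistics section of the protocol article states: "Data distribution will be tested by the Kolmogorov-Smirnov analysis". The next sentence ties the summary to the result: "Normally distributed data will be presented as mean and standard deviation (SD) and skewed data as median (interquartile range". The one after it ties the test to the same result, with rank tests where the distribution is not normal: "the paired and unpaired *t* test will be used for normally distributed data and the Wilcoxon signed rank test and Mann-Whitney *U* test for skewed". The significance rule is "A *P* value < 0.05 will be considered significant".

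The same section then names tests that do not depend on the pre-test: an unpaired t test for PPC, a two-way repeated-measures ANOVA for PCT levels, and chi-square for SOFA, ICU days, hospital stay and mortality.

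On size, the section on study arms gives 40 patients and says "An equal number of patients will be randomized into the two groups". The section on randomization describes a "computer-generated blocked randomization list with 10 blocks of four patients per block".

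**The concern.** A normality test in a sample of 20 has little power against moderate skewness, so a pass says little about the shape of the data. Under this rule a pass still fixes the summary and, where no test is named, the test. The effect measure (a difference in means or a rank comparison) is then chosen by the data and not in advance.

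The rule can also return different answers for one variable. PCT is sampled at seven times in two arms. Judged separately, that is 7 × 2 = 14 verdicts, and the reported course could switch between mean (SD) and median (IQR) along the way.

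The comparisons exposed to the choice of test are not trivial. Oxygenation belongs to the first objective, PaO2/FiO2 is calculated every 6 h after surgery, and the change in PCT between T0, T24 and T48 is part of a primary outcome with no test of its own.

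**Working it through.** **Sample size.** 10 blocks × 4 = 40, and 40/2 = 20 per arm at 1:1. This agrees with the stated total. The article gives no power calculation and no distribution for any outcome, so every shape below is an assumption, shown as a range.

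**Set-up.** Kolmogorov-Smirnov test with mean and SD estimated from the sample, pre-test level 5% (assumed), n = 20. Critical D is 0.192 with the Lilliefors correction and 0.294 without it. Data are log-normal. Let p be the probability that one arm's skewness is missed. If the test is run per arm, both arms pass with probability p² and the arms disagree with probability 2p(1 − p).

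Each cell is Lilliefors / uncorrected:

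| Log-SD (skewness) | One arm missed, p | Both arms pass, p² | Arms disagree, 2p(1 − p) |
|---|---|---|---|
| 0.5 (1.75) | 65.9% / 98.5% | 43% / 97% | 45% / 3% |
| 0.75 (3.26) | 40.1% / 92.6% | 16% / 86% | 48% / 14% |
| 1.0 (6.18) | 20.9% / 80.4% | 4% / 65% | 33% / 32% |

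Example: at log-SD 0.5 with Lilliefors, 0.659² = 0.434 and 2 × 0.659 × 0.341 = 0.449. If both arms are pooled (n = 40), the miss rates fall to 39% / 93%, 11% / 68% and 2% / 36%.

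**Type I error.** The two-stage procedure (t test if both arms pass, otherwise Mann-Whitney) rejects in 4.8% to 5.9% of null samples over the skewed shapes tried. Among samples in which both arms pass Lilliefors, the t test rejects in 6% to 13%. That subset is small when skewness is strong, so the overall rate hardly moves.

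**Power, log-SD 1.0, 20 per arm.**

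| True ratio | t test | Gated, uncorrected | Gated, Lilliefors | Mann-Whitney | t test on logs |
|---|---|---|---|---|---|
| 2.0 | 40% | 51% | 55% | 55% | 57% |
| 2.5 | 62% | 75% | 79% | 79% | 81% |

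The last column can be checked directly. The noncentrality is ln(ratio)/log-SD × √(n/2). At ratio 2.0 it is 0.693 × √10 = 2.19, and at 2.5 it is 0.916 × √10 = 2.90. Against a critical t of 2.02 on 38 degrees of freedom, these give 57% and 81%.

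Loss from gating:
- Lilliefors against Mann-Whitney: 55 − 55 = 0 and 79 − 79 = 0.
- Lilliefors against the log-scale t test: 57 − 55 = 2 and 81 − 79 = 2.
- Uncorrected against Mann-Whitney: 55 − 51 = 4 and 79 − 75 = 4.
- Uncorrected against the log-scale t test: 57 − 51 = 6 and 81 − 75 = 6. A simulation run that put the log-scale figure at 82% gives 82 − 75 = 7.

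The range is therefore about 0 to 7 points. It belongs to the log-normal assumption. For exponential data and a two-fold ratio the t test has 52% power and Mann-Whitney 45%, with gating at 47% (Lilliefors) or 52% (uncorrected), so there gating loses nothing against Mann-Whitney.

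**The case against.** A reader might infer that the pre-test decides how the trial's main outcomes are tested, so that skewed PCT, ICU days and hospital stay would be compared as if normal because the pre-test missed the skewness. The Statistics section does not support this. Those outcomes, with PPC and SOFA, have named tests that apply whatever the pre-test shows, and for the continuous ones among them it can change only the summary. Whether a t test suits PPC, or chi-square suits days and scores, is a separate and more serious question.

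The power figures also model two- to two-and-a-half-fold ratios of log-normal data. That resembles PCT levels, which go to ANOVA, more than the physiological measures that the gate does govern. If those are roughly symmetric, the pre-test does little harm. This stands, and it is why the power loss is only indicative.

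Finally, the version of the test, its level, and per-arm or pooled use are details that an article may leave to a fuller document, so their absence is no fault. They matter here only because they set the range. Under the Lilliefors version strong skewness is usually found: at log-SD 1.0 both arms pass in only 4% of trials. Moderate skewness is still missed often under either version when the test is run per arm, so the point does not depend on the missing detail.

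**Conclusion.** The concern holds with limited scope and minor weight. The stated rule makes the summary of every continuous variable, and the test for comparisons without a named method, depend on a test with low power at this sample size. Under log-normal data with log-SD 0.5 to 1.0, one arm's skewness is missed in about 21% to 66% of samples (Lilliefors) or 80% to 99% (uncorrected). If the rule is applied per arm with Lilliefors, the two arms would be classed differently in about 33% to 48% of trials.

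The main harm is unstable and possibly misleading reporting. The documents and the calculations do not support a claim of inflated false positives, because overall type I error stays near 5%. Nor do they support a large loss of power: it is about 0 to 7 points by version and comparator, and about 0 against Mann-Whitney with Lilliefors. All of this rests on assumed shapes, a 5% pre-test level and 20 evaluable patients per arm.

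**What to change.** Delete the normality pre-test and name the summary, test and effect measure for each outcome in advance:

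- **PCT levels and changes:** analyse on the log scale and report geometric mean ratios with 95% CI. The Study endpoints section already expects PCT to fall by about half each day, which is a proportional change, so no pre-test is needed to choose this scale.
- **ICU days, hospital stay and SOFA:** summarise by median (IQR) and compare by Mann-Whitney with a Hodges-Lehmann difference and 95% CI. This also replaces the stated chi-square test for these outcomes.
- **Roughly symmetric physiological measures:** use mean (SD) and t-based methods, listing the variables by name.

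Swapping in a stronger normality test would not be enough. At n = 20 Shapiro-Wilk still misses log-normal skewness in 49% of samples at log-SD 0.5 and 7% at 1.0.

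The cost is analysis wording only, with no new data. The article says the analysis follows completion of the trial and plans no interim look, so the change can be fixed before any comparison is made.

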### Study endpoints

The primary outcome variables are PPC and PCT kinetics. PPC are defined as new infiltrates or atelectasis on a chest X-ray, abnormal breathing sounds on auscultation, respiratory failure defined as PaO_2_/FiO_2_ < 300 or the need for noninvasive or invasive ventilatory support within the first three postoperative days. PCT kinetics will be evaluated during and after surgery. Blood samples will be taken at 0, 2, 6, 12, 24, 48 and 72 h after surgical incision. According to recent data it is expected that PCT values will peak at approximately 24 h after surgery and that they should decline by approximately 50% daily in the case of an uneventful postoperative course. Therefore, in addition to the absolute values the change between T_0_–T_24_–T_48_ will also be evaluated [16, 22].

Secondary outcome variables are extrapulmonary complications: incidence of circulatory failure, gastrointestinal and renal dysfunction, hematologic and coagulation disorders and infection (Table 1).

**Table 1 Tab1:** Secondary endpoints

Endpoint	Time frame	Detailed description
Circulatory failure	28 days	Hypotension – MAP < 65 mmHg
		Severe cardiac arrhythmia – 40/min < HR > 150/min
		ScvO_2_ < 70%
		dCO_2_ > 7 mmHg
		Serum lactate > 2 mmol/L
		Severe metabolic acidosis (actual bicarbonate < 18 mmol/L)
		Acute coronary syndrome
		Acute left ventricular failure
		Pulmonary embolism
		Cardiac arrest
Gastrointestinal dysfunction	28 days	Constipation
		Ileus
		Anastomotic leakage
		Reoperation
		Disorders of liver function
Renal dysfunction	28 days	RIFLE criteria
Hematologic and coagulation disorders	28 days	Severe bleeding
		Coagulopathy – INR > 1.5
Infection	28 days	Any infection except from pneumonia

*MAP* mean arterial pressure, *HR* heart rate, *ScvO*
_*2*_ central venous oxygen saturation, *dCO*
_*2*_ central venous-to-arterial carbon dioxide gap, *INR* International Normalized Ratio

Tertiary endpoints are intensive care unit (ICU) days, in-hospital stay, in-hospital and 28-day mortality.

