### Selection of the participants

Patients with bladder cancer scheduled for open radical cystectomy and urinary diversion will be screened and recruited during routine perioperative assessment. Participants fulfilling the inclusion criteria will be asked for their signed informed consent. Withdrawal of consent may be initiated by the participant at any time during the trial.

Inclusion criteria are age over 18 years, patients with bladder cancer undergoing radical cystectomy and urinary diversion (ileal conduit or orthotopic bladder substitute) and provision of signed informed consent.

Exclusion criteria are age below 18 years, American Society of Anesthesiologists (ASA) physical status IV, history of severe chronic obstructive pulmonary disease (COPD, GOLD grades III or IV), history of severe or uncontrolled bronchial asthma, history of severe restrictive pulmonary disease, pulmonary metastases, history of any thoracic surgery, need for thoracic drainage before surgery, renal replacement therapy prior to surgery, congestive heart failure (NYHA grades III or IV), extreme obesity (Body Mass Index, BMI > 35 Kg/m^2^) and lack of patient’s consent.

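### The repeated-measures ANOVA named for primary PCT cannot use incomplete series, and their handling is left until the missing pattern is seen, so intention-to-treat is not secured for PCT

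*Protocol article*

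**What the plan says.** All references are to the protocol article.

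- **Study endpoints:** "The primary outcome variables are PPC and PCT kinetics". The sampling schedule is: "Blood samples will be taken at 0, 2, 6, 12, 24, 48 and 72 h after surgical incision".
- **Preoperative assessment and admission:** on the day before surgery, ahead of randomisation in the order described, "a blood sample will be taken from included patients for baseline levels of PCT". This is T0.
- **Selection of the participants:** "Withdrawal of consent may be initiated by the participant at any time during the trial".
- **Statistics, test for PCT:** "A two-way, repeated-measures analysis of variance (two-way RM ANOVA) will be used to compare" the two groups on serum PCT. On software: "IBM SPSS 20.0 statistical software will be used for analysis". No SPSS procedure is named.
- **Statistics, principle:** "Statistical analysis will be conducted on an intention-to-treat basis".
- **Statistics, missing data:** "before starting the data analysis, the mechanism and pattern of missing data will be evaluated". The findings are then to decide whether the results were affected and what to do about it. No imputation method, mixed model or rule for incomplete PCT series is given.
- **Blinding, data collection, randomization and record-keeping:** the trial is single-blinded, and the blinded party is the participant.

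**The concern.** The article fixes three things for a primary outcome: a test, an analysis principle and a missing-data process. They do not fit together well.

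The classical two-way repeated-measures ANOVA treats a patient's PCT values as one block. If one value is absent the block cannot be used, and the ordinary result is that the patient leaves the analysis with every valid value. Someone who withdraws after 24 h, dies before 72 h or simply misses the 12 h draw would contribute nothing. The principle stated in the same section asks for all randomised patients to be compared as allocated.

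The missing-data process could close this gap, but as written it only postpones the decision. The method is to be chosen after the pattern has been examined, by a research team that is not described as blinded. Which patients count in a primary comparison could then be settled when allocation and results can be known.

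Two things are at stake. One is precision, because 40 patients leave little to spare. The other is comparability of the arms, because samples lost to death, deterioration or withdrawal are unlikely to be lost independently of the inflammatory response being measured.

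**Working it through.** **Figures in the article.** There is no missing-sample or dropout rate, so there is no stated figure to reproduce. The sample size is consistent with the randomisation list: 10 blocks × 4 = 40, or 20 per arm at 1:1.

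**Inputs**
- N = 40 (Study arms and assigned intraoperative interventions).
- k = 7 PCT draws (Study endpoints). k = 6 if T0 is always present, which is plausible because it is taken the day before surgery.
- m = chance that any one sample is missing. This is an assumption: 1%, 2%, 3% or 5%, independent between samples.

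**Patients lost if nothing is added to the ANOVA.** Expected loss = N × [1 − (1 − m)^k].

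| m | k = 6: share lost | of 40 | k = 7: share lost | of 40 |
|---|---|---|---|---|
| 1% | 1 − 0.941 = 5.9% | 2.3 | 1 − 0.932 = 6.8% | 2.7 |
| 2% | 1 − 0.886 = 11.4% | 4.6 | 1 − 0.868 = 13.2% | 5.3 |
| 3% | 1 − 0.833 = 16.7% | 6.7 | 1 − 0.808 = 19.2% | 7.7 |
| 5% | 1 − 0.735 = 26.5% | 10.6 | 1 − 0.698 = 30.2% | 12.1 |

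The chance that at least one patient is lost is 1 − (1 − m)^(40k). At m = 1% this is 1 − 0.99^240 = 91% for k = 6 and 1 − 0.99^280 = 94% for k = 7.

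**If losses cluster within patients.** Independence gives more incomplete patients than the same number of missing samples concentrated in a few people. If the only cause is whole-patient dropout of 5% to 20%, then 40 × 0.95 = 38 down to 40 × 0.80 = 32 patients remain.

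**Precision.** At a single time point, with 80% power and two-sided 0.05 (the article does not state sidedness), the detectable standardised difference is about (1.96 + 0.84) × √(2/n). For n = 20 per arm it is 0.89. For n = 14 per arm, roughly the 5% row, it is 1.06. This is a rough guide, not the power of the ANOVA.

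**Direction of bias.** Suppose, purely for illustration, that 30% of controls and 10% of study-group patients have a complicated course that raises log PCT by 1.2.
- All patients kept: 1.2 × (0.10 − 0.30) = −0.24.
- Half of the complicated patients in both arms excluded: 1.2 × (0.05/0.95 − 0.15/0.85) = 1.2 × (0.0526 − 0.1765) = −0.15, which is weaker.
- The same loss in the study group only: 1.2 × (0.0526 − 0.30) = −0.30, which is stronger.

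These inputs are invented. They show only that exclusion can move the difference either way.

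**The case against.** A reader might infer that the plan commits to deleting incomplete patients and so contradicts its own intention-to-treat statement. The article does not support that. It never specifies complete-case analysis, it names SPSS but no procedure, and it undertakes to assess missing data and decide how to manage them. Imputation before the ANOVA, or a mixed-model fit of the same group-by-time design, remains open. Analysing patients as allocated and handling missing values are also separate questions. They collide only if deletion is the handling finally chosen.

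It can further be said that detail on missing data normally sits in a fuller protocol or analysis plan, which is not shown. That is fair as regards the imputation method. It does not cover the choice of primary test, which the article does make. A mixed model is a different and better-suited choice, not a missing detail.

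Exposure may also be small. All draws fall within 72 h of incision. Patients have a central venous catheter and go to the ICU, blood gases are taken every 6 h to 72 h after surgery, a study nurse is responsible for the samples, and an external physician checks completeness. This stands, and it makes the lower rows of assumed loss more credible than the 5% row.

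Finally, a reader might infer that exclusion would pull the PCT difference toward zero. That holds only under particular assumptions about who is lost from which arm, and the article gives no information on this.

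**Conclusion.** The point holds in a limited form. The test named for a primary outcome has no built-in way to use an incomplete PCT series, and what will be done about such series is to be decided after the pattern has been seen, without staff blinding. The intention-to-treat basis is therefore unsecured for PCT, though not broken.

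The possible loss is about 2 to 11 of 40 patients with six draws at risk, or 3 to 12 with seven, for assumed independent loss of 1% to 5% per sample. It would be smaller if losses cluster in few patients, and zero if sampling is complete. The rates are assumptions and cannot be derived from the article. No direction of bias is established. This is a real but moderate weakness in a primary analysis, and it is cheap to remove.

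**What to change.** In Statistics, replace the two-way repeated-measures ANOVA for PCT, before the data are examined, with a linear mixed model for repeated measures:

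- **Terms:** group, time and group-by-time, fitted with the MIXED procedure in SPSS.
- **Data:** every available PCT value from all randomised patients, analysed as allocated, including values taken before death or withdrawal where consent allows.
- **Covariance:** state the structure in advance, with a simpler fallback. An unstructured matrix for seven times has 7 × 8 / 2 = 28 parameters, which is a lot for 20 patients per arm and may not converge.
- **Death and deterioration:** state how samples lost for these reasons are treated.
- **Sensitivity analysis:** add one simple analysis, for example repeating the comparison with those lost values set to a high PCT level fixed in advance.

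The cost is a few sentences, with the same software and no extra patients or samples. With complete data, little is given up compared with the ANOVA. The small downside is that the model assumes values are missing at random given the observed PCT. That assumption is least secure for samples lost to death or deterioration, which is why the last two items are needed.

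### Procalcitonin, a primary outcome expected to halve daily, is assigned a two-way RM ANOVA with no log scale and no baseline covariate, which can cost power

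*Protocol article*

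**What the plan says.** Study endpoints sets the status of the marker: "The primary outcome variables are PPC and PCT kinetics". The same section expects a peak roughly 24 h after surgery, after which values "decline by approximately 50% daily in the case of an uneventful postoperative course". It adds that the trial will evaluate, "in addition to the absolute values the change between" T0, T24 and T48.

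Statistics names the test: "A two-way, repeated-measures analysis of variance (two-way RM ANOVA) will be used to compare the groups’ serum PCT levels". It does not give the scale, the role of T0, the effect to be tested (group or group-by-time) or a sphericity correction. The same section has a distribution check, "Data distribution will be tested by the Kolmogorov-Smirnov analysis", but it leads to rank tests only for paired and two-group comparisons. No alternative to the RM ANOVA is given for PCT.

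The first sample is described in two ways. Study endpoints says "Blood samples will be taken at 0, 2, 6, 12, 24, 48 and 72 h after surgical incision", and Objectives of the study lists the same times. Preoperative assessment and admission says that on the day before surgery, ahead of randomisation, "a blood sample will be taken from included patients for baseline levels of PCT", and labels this sample T0. Intraoperative care then lists only the samples from 2 to 72 h.

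**The concern.** A marker that halves each day changes by a constant ratio, not a constant amount. Take assumed medians of 1.2, 0.6 and 0.3 at 24, 48 and 72 h. The absolute falls are 0.6 and then 0.3, but both are the same log change, ln 0.5 = -0.693. In absolute units the spread grows with the level, so a few high responders around the peak carry most of the weight.

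T0 is drawn before randomisation and cannot carry a treatment effect. Its efficient use is as a covariate, because adjustment removes between-patient variation that T0 predicts.

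At stake is the power of a primary comparison in a trial of 40 patients. The named analysis also leaves the scale and the tested effect open, and the Statistics section places the analysis after the trial is complete.

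**Working it through.** **Figure to reproduce.** There is none. The article gives no effect size, SD or power for PCT, so everything below rests on assumptions.

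**Inputs from the protocol.** 40 patients, 1:1, so 20 per arm; seven sampling times; peak near 24 h, then about 50% decline per day; significance at 0.05 (two-sided assumed).

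**Assumed inputs.** Log-normal PCT with medians 0.05, 0.06, 0.3, 0.8, 1.2, 0.6 and 0.3 at the seven times. Post-baseline log SD 0.5, 0.8 or 1.1, with T0 log SD 0.7 times that. Post-baseline correlation AR(1) 0.8 or exchangeable 0.7. Correlation of T0 with later values 0, 0.3 or 0.6. True ratio 1.0 (null) or 0.5, phased in as 25%, 60%, then 100% of the log effect over the first 12 h. 1,500 simulated trials per scenario. The Monte Carlo error is sqrt(0.05 x 0.95 / 1500) = 0.6 points at 5% and sqrt(0.5 x 0.5 / 1500) = 1.3 points at 50%.

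**Tests compared.** (a) RM ANOVA group effect in absolute units over all seven times, equivalent to a t test on each patient's mean. (b) Its group-by-time test, uncorrected and Greenhouse-Geisser corrected. (c) ANCOVA of mean post-incision log PCT on log T0.

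**Type I error (ratio 1.0), range over all scenarios**
- Group effect, absolute units: 3.1 to 6.2%
- Group-by-time, uncorrected: 9.1 to 13.1% (mean epsilon 0.28 to 0.32)
- Group-by-time, Greenhouse-Geisser: 2.0 to 5.7%
- Log ANCOVA: 4.5 to 5.7%

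**Power (ratio 0.5), in %, as AR(1) / exchangeable**

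| Log SD | T0 correlation | Group effect, absolute units | Log ANCOVA | Difference, points |
|---|---|---|---|---|
| 0.5 | 0 | 99.3 / 99.1 | 98.5 / 97.2 | -0.8 / -1.9 |
| 0.5 | 0.3 | 98.7 / 99.0 | 98.9 / 98.8 | +0.2 / -0.2 |
| 0.5 | 0.6 | 99.0 / 98.8 | 100 / 100 | +1.0 / +1.2 |
| 0.8 | 0 | 72.1 / 73.1 | 75.7 / 69.1 | +3.6 / -4.0 |
| 0.8 | 0.3 | 70.8 / 71.1 | 77.9 / 73.7 | +7.1 / +2.6 |
| 0.8 | 0.6 | 72.5 / 70.7 | 96.6 / 92.5 | +24.1 / +21.8 |
| 1.1 | 0 | 38.4 / 39.1 | 44.9 / 45.0 | +6.5 / +5.9 |
| 1.1 | 0.3 | 38.1 / 38.9 | 52.5 / 48.9 | +14.4 / +10.0 |
| 1.1 | 0.6 | 35.7 / 40.7 | 78.7 / 70.1 | +43.0 / +29.4 |

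**Closed-form check of the ANCOVA column.** The mean log effect is (0.25 + 0.6 + 4 x 1)/6 x ln 0.5 = 0.808 x (-0.693) = -0.560. Let r be the average of all entries of the 6 x 6 post-baseline correlation matrix: 0.680 for AR(1) and 0.750 for exchangeable. Then SE = sqrt(SD^2 x (r - rho^2) x 2/20), where rho is the T0 correlation. With SD 0.8, rho 0.6 and AR(1): SE = sqrt(0.64 x 0.320 / 10) = 0.143 and 0.560/0.143 = 3.9, a power of about 97% on 37 df (simulated 96.6%). With rho 0: SE = sqrt(0.64 x 0.680 / 10) = 0.209 and 0.560/0.209 = 2.7, about 74% (simulated 75.7%). The gap between the two shows how much comes from the T0 adjustment.

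**T0 as a repeated time.** Dropping T0 from the RM ANOVA in absolute units changes group-effect power by at most about 1 point, because T0 is near zero in this profile. It does not cure the uncorrected group-by-time test, which still rejects in 7.7 to 11.4% of null trials.

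**The case against.** The strongest reply is that the Statistics section never says that PCT stays untransformed, that T0 is one of the repeated levels, or that no sphericity correction will be made. These are inferences from the mention of serum levels and absolute values and from the list of times, and an unseen analysis plan may settle them. That stands as a limit on the claim. What remains is that the article itself names a test for a primary outcome, and that test does not fit the proportional decline the article expects.

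A reader might infer more, and the documents do not support it:
- *The error rate of the PCT test is misstated.* This holds only for an uncorrected group-by-time test, which the protocol does not commit to. The cause is non-sphericity, not T0.
- *Keeping T0 as a time point dilutes the group effect.* In absolute units it costs almost nothing. The loss comes from the scale and the missing adjustment.
- *RM ANOVA discards incomplete patients against intention to treat.* With seven samples, an independent missing rate of 2% would touch 40 x (1 - 0.98^7) = 5.3 patients, and 5% would touch 40 x (1 - 0.95^7) = 12.1. Those rates are assumed, and the Statistics section provides for a review of missing data and how to manage it, so complete-case deletion is not the stated plan.
- *The Kolmogorov-Smirnov check will miss the skewness.* For log-normal data with n = 20 and log SD 0.7 to 1.0, the plain test detects it 5 to 21% of the time, but the Lilliefors form 54 to 80%. The protocol does not say which is used.
- *Log-scale group-by-time is the test to prefer.* If the treatment ratio is constant after surgery, that interaction is only T0 against the rest. In a simulation with ratio 0.6, its power was 54 to 97% with T0 kept as a time and sharing the patient effect, and 4 to 5% once T0 was removed from the outcomes.

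**Conclusion.** The point holds as a should-fix. For a primary outcome expected to halve daily, the protocol names an RM ANOVA on PCT levels with no log scale and no adjustment for the pre-randomisation sample.

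The cost is conditional. At log SD 0.5 all methods have about 95% power or more, so nothing is gained. With T0 uncorrelated with later values, the difference runs from -4 to about +6 points. With T0 correlation 0.6 and log SD 0.8 to 1.1, the gain is about 20 to 30 points in three of the four scenarios and 43 in the fourth. The group effect and the Greenhouse-Geisser test keep their error rate near or below 5 to 6%.

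These sizes rest on assumed log-normal data, SDs, correlations and a 50% reduction, because the protocol gives none of these.

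Separately, the sample timed at 0 h from incision and the day-before T0 cannot both be the baseline as described, and the planned T0-T24-T48 change depends on which is meant.

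**What to change.** In Statistics, replace the PCT sentence with a linear mixed model on log PCT at the six post-incision times (2, 6, 12, 24, 48 and 72 h). Include group, time, group x time and log T0 as covariate, and use all available samples. Name the baseline-adjusted overall post-incision group effect as the primary PCT test, with group x time as secondary. Report geometric mean ratios with 95% CI. Express the T24-T48 change as a log ratio, which reads directly as a percentage decline against the expected halving.

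Reconcile the 0 h sample in Objectives of the study and Study endpoints with the day-before T0 in Preoperative assessment and admission, so that T0 has one definition.

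The cost is wording. SPSS 20, the software already named, fits this model, and no further patients or samples are needed. Results will be read as ratios rather than absolute differences, and little or no power is gained if T0 does not predict later PCT.
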